### Adverse Events

#### *Definition of an Adverse Event (AE):*

Any untoward medical occurrence in a subject to whom a medicinal product has been administered, including occurrences which are not necessarily caused by or related to that product.

An AE can therefore be any unfavourable and unintended sign (including a clinically significant abnormal finding), symptom or disease temporally associated with the use of a medicinal product, whether or not considered related to the medicinal product.

All AEs should be treated appropriately. Treatment may include one or more of the following:

- no action taken (i.e. further observation only)
- study drug dosage adjusted/temporarily interrupted
- study drug permanently discontinued due to this adverse event
- concomitant medication given
- non-drug therapy given
- patient hospitalized/patient's hospitalization prolonged.

The action taken to treat the adverse event will be recorded on the AE form. Once an adverse event is detected, it will be followed until its resolution or until it is judged to be permanent, and assessment will be made at each visit (or more frequently, if necessary) of any changes in

severity, the suspected relationship to the study drug, the interventions required to treat it, and the outcome.

Information about common side effects already known about the study drug will be included in the patient informed consent and will be discussed with the patient during the study as needed.

#### Severity, relationship of event to study drug, and outcome

The **severity** of a clinical adverse event is to be scored according to the following scale:

| Grade | Severity         | Description                                                     |
|-------|------------------|-----------------------------------------------------------------|
| 1     | Mild             | Awareness of sign or symptom, but easily tolerated              |
| 2     | Moderate         | Discomfort enough to cause interference with usual activity     |
| 3     | Severe           | Incapacitating with inability to work or perform usual activity |
| 4     | Life-threatening | Patients at risk of death at the time of the event              |

All adverse events will be assessed and documented by the local principal investigator using a toxicity table that will be developed as SOP. All grade 3-4 toxicities are considered **serious**.

Changes in the severity of an AE should be documented to allow an assessment of the duration of the event at each level of severity. Adverse events characterized as intermittent will provide documentation of onset and duration of each episode.

The **relationship** of an adverse event to study drug is to be assessed according to the following definitions:

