#### **Serious Adverse Events (SAE)**

A SAE is an adverse event that:

- Results in death
- Is life threatening
- Requires hospitalization or prolongation of existing hospitalization
- Results in persistent or significant disability or incapacity or
- Consists of a congenital anomaly or birth defect

The Principal Investigators at each study site will be responsible for recording, management, and reporting of the AEs and SAEs. They must be recorded in the AE/SAE CRF with the following information:

- The severity grade (mild, moderate, severe)
- Relationship to the study drug(s) (suspected/not suspected)
- Duration (start and end dates or if continuing at final exam)

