#### **Monitoring and reporting of Adverse Events**

Safety will be evaluated in the mother, the foetus and the newborn. Active safety monitoring will consist in daily phone visits to study participants from the initiation of treatment administration to assess drug tolerability and record all Adverse Events (AEs). In addition, a health facility-based passive surveillance system will be established to capture unscheduled visits of participants during follow-up.

The Principal Investigators (PI) at each study site will be responsible for recording, managing, and reporting of the AEs and SAEs as per study protocol. All AEs will be recorded in the AE form, and the DSMB will agree which SAEs and in what time frame will be reported.

All SAEs will be recorded on the SAE form and will be reported within 24 or 48 hours to the sponsor's (ISGlobal) Safety Coordinator, the CRO Dynamic Solutions, and to the DSMB as per study protocol. A flowchart will be provided to each study site to train the procedures for assessing AEs and reporting requirement according to severity and expectedness as well as persons responsible for recording and reporting of AEs/SAEs.

All participants enrolled in the trial will be educated at the beginning of the study on how to and whom to contact if they experience any untoward event and/or get admitted to the hospital.

In addition, Interim Safety Reports and Annual Safety Reports will be prepared by the Safety Coordinator and the CRO Dynamic Solutions and distributed to the local Ethic Committee, Sponsor, and DSMB as agreed in the study protocol.

The CRO Dynamic Solutions will ensure that AEs and SAEs are reported in compliance with International Conference on Harmonisation (ICH) Good Clinical Practice (GCP) guidelines and current international legislation during COVID-19 pandemic.

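### Two rules decide when an adverse event is serious: the grading text makes every grade 3 event serious, but the SAE definition is outcome-based and does not

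*Protocol*

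**What the plan says.** All of the text is in Protocol section 5.e (Safety).

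- *Severity, relationship of event to study drug, and outcome* sets a four-grade scale. Grade 3 (severe) is "Incapacitating with inability to work or perform usual activity" and grade 4 (life-threatening) is "Patients at risk of death at the time of the event". The section then says "All grade 3-4 toxicities are considered" serious, with that last word in bold.
- *Serious Adverse Events (SAE)* defines an SAE by five outcomes. The first is "Results in death" and the third is "Requires hospitalization or prolongation of existing hospitalization". The others are a threat to life, lasting or significant disability or incapacity, and a congenital anomaly or birth defect. It names no grade and does not refer back to the grading rule.
- The same section lists what the AE/SAE form must record, beginning with "The severity grade (mild, moderate, severe". That is three levels.
- *Monitoring and reporting of Adverse Events* says "the DSMB will agree which SAEs and in what time frame will be reported". Its next paragraph says "All SAEs will be recorded on the SAE form and will be reported within 24 or 48 hours".

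Elsewhere, *Secondary endpoints* includes the frequency and severity of maternal adverse events (item 6), and *Statistical analysis populations* has safety analysed by arm.

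**The concern.** Severity and seriousness are different attributes. Severity is how intense an event is; seriousness is whether it has one of a fixed set of consequences. The grading section derives the second from the first, while the SAE section defines it independently. Both are current text, so a site that follows either one complies with the protocol.

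SAE status decides whether an SAE form is completed and an expedited report sent, and it is the entry condition for a SUSAR. The principal investigator at each of five hospitals makes the classification. If they read the text differently, the trial's SAE count mixes two definitions.

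The three-level severity field raises a separate problem. If the form is built as listed, grades 3 and 4 cannot be told apart in that field, and severity is part of a named endpoint.

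**Working it through.** No arithmetic applies, and there is no stated figure to reproduce. The check sets the two rules side by side for each type of event.

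| Event | Grading rule | SAE definition | Conflict? |
|---|---|---|---|
| Grade 4 | Serious | SAE (threat to life) | No |
| Grade 3, admitted to hospital or stay prolonged | Serious | SAE (hospitalisation) | No |
| Grade 3 with lasting or significant incapacity | Serious | SAE (incapacity) | No |
| Grade 3, transient, managed at home, incapacity not judged significant | Serious | No clear criterion met | **Yes** |
| Grade 1-2 leading to admission | Not addressed | SAE (hospitalisation) | No |
| Congenital anomaly, any grade | Serious only if grade 3-4 | SAE | No |

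In the last two rows the SAE list goes further than the grading sentence. That sentence does not say lower grades are non-serious, so there is no contradiction. The conflict is confined to the fourth row. An example is a woman kept from her usual activities for a day by vomiting and managed at home.

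**Severity levels.** The scale has four: mild, moderate, severe, life-threatening. The form's listed field has three, and life-threatening is the one left out. The other listed items are relationship and duration. Which SAE criterion was met is not among them, so later reclassification would rely on other records, such as the action taken that is recorded on the AE form (*Adverse Events*), which can include hospitalisation.

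**Reporting.** One sentence leaves it to the DSMB to agree which SAEs are reported and when. The next paragraph has all SAEs reported within one of two time limits, without saying when each applies.

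**The case against.** The case for leaving the text alone has real force.

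- **Overlap.** Grade 3 is described as incapacitating, and the SAE list accepts incapacity that is either persistent or significant, so persistence is not required. Many grade 3 events could qualify. This stands, and it limits the conflict to the fourth row of the table, but it does not remove it: the grading sentence covers all grade 3 toxicities, while the SAE list requires a judgement.
- **Deliberate caution.** Treating every grade 3-4 event as serious may be intended in pregnant women. If so, the SAE definition should include it, and it does not.
- **Later documents.** A toxicity table is to be an SOP, the eCRF is still to be developed, and each site will receive a flowchart and training. It therefore cannot be said that grade 4 will be impossible to enter. The DSMB agreement and the flowchart can also settle the two time limits, so that point is loose wording. But an SOP cannot decide which of two protocol sentences governs seriousness.

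A reader might infer more than the protocol supports:

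- **That the SAE comparison between arms is undefined.** The protocol names no such comparison, and it does give an explicit SAE definition.
- **That the SAE rate on hydroxychloroquine is inflated.** *HCQ side effects* names gastrointestinal effects as major short-term events but gives no grade 3 rates. Classification is blinded, so differences between sites mainly add noise. If grade 3 events were more common on hydroxychloroquine, that would be a true difference in toxicity; only its label would be in question.
- **That the expedited channel would be flooded.** No event rate in the protocol supports this.
- **That gastrointestinal events would become SUSARs.** A SUSAR must be undocumented in the product information or protocol, and *HCQ side effects* documents these events.

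**Conclusion.** The point holds as an internal inconsistency. Transient grade 3 events that were not hospitalised and caused no significant incapacity are serious under one rule and not clearly SAEs under the other. SAE counts and expedited reporting can therefore differ between the five sites. Grade 4 is not in conflict on seriousness. The three-level field against the four-grade scale is a second, smaller mismatch that touches a secondary endpoint.

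The effect cannot be sized from the protocol. With purely assumed rates of 3-10% on hydroxychloroquine and 1-3% on placebo for such events, the gap between arms could be anything from 3 - 3 = 0 to 10 - 1 = 9 percentage points. That range is too wide to support a claim of distortion. No efficacy analysis is affected. The conclusion rests only on the wording of the two sections and on the word serious in the grading sentence meaning what it means in the SAE definition.

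**What to change.** 1. Reconcile the grading sentence with the SAE definition so that one rule decides seriousness. One way is to let the five outcome criteria define an SAE and to record grade 3-4 events as a separate flagged category, tabulated by arm and not counted as SAEs unless a criterion is met. If the wider rule is intended, add it to the SAE definition instead.
2. Use the same four severity grades in the AE/SAE form fields as in the grading scale.
3. Reconcile the two reporting sentences: state which time limit applies to which SAEs, and what the DSMB's agreement covers.

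The cost is a few sentences and one pick-list, with no added patients, visits or samples.

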##### *Definitely unrelated:*

It should be reserved for those events which occur prior to test drug administration (e.g., washout or single-blind placebo) or for those events which cannot be even remotely related to study participation (e.g. injury caused by a third party).

##### *Unlikely:*

There is no reasonable temporal association between the study drug and the suspected event and the event could have been produced by the subject's clinical state or other modes of therapy administered to the subject.

##### *Possible:*

The suspected adverse event may or may not follow a reasonable temporal sequence from study drug administration but seems to be the type of reaction that cannot be dismissed as unlikely. The event could have been produced or mimicked by the subject's clinical state or by other modes of therapy concomitantly administered to the subject.

##### *Probable:*

The suspected adverse event follows a reasonable temporal sequence from study drug administration, abates upon discontinuation of the drug, and cannot be reasonably explained by the known characteristics of the subject's clinical state.

#### *Definitely related*

It should be reserved for those events, which have no uncertainty in their relationship to test drug administration: this means that a re-challenge was positive.

The **outcome** of each AE must be assessed according to the following classification:

- Completely recovered: the patient has fully recovered with no observable residual effects
- Not yet completely recovered: improvement in the patient's condition has occurred, but the patient still has some residual effects
- Deterioration: the patient's overall condition has worsened
- Permanent damage: the AE has resulted in a permanent impairment
- Death: the patient died due to the AE
- Ongoing: the AE has not resolved and remains the same as at onset
- Unknown: The outcome of the AE is not known because the patient did not return for follow-up (lost to follow-up)

#### **Serious Adverse Events (SAE)**

A SAE is an adverse event that:

- Results in death
- Is life threatening
- Requires hospitalization or prolongation of existing hospitalization
- Results in persistent or significant disability or incapacity or
- Consists of a congenital anomaly or birth defect

The Principal Investigators at each study site will be responsible for recording, management, and reporting of the AEs and SAEs. They must be recorded in the AE/SAE CRF with the following information:

- The severity grade (mild, moderate, severe)
- Relationship to the study drug(s) (suspected/not suspected)
- Duration (start and end dates or if continuing at final exam)

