#### Secondary endpoints

##### Maternal/Foetal

1. Incidence of COVID-19 disease during pregnancy
2. Incidence of COVID-19-related admissions
3. Incidence of all-cause admissions
4. Incidence of all-cause outpatient attendances
5. Mean duration of symptoms-signs of COVID-19

6. Frequency and severity of adverse events
7. Incidence of preeclampsia
8. Incidence of gestational diabetes
9. Incidence of SARS-CoV-2 infections during pregnancy
10. Prevalence of intrauterine growth restriction (<10th centile according to local standards) (21)
11. Maternal mortality rate

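### The protocol grades adverse event severity on four levels but tells sites to record it on three, with no entry for life-threatening events

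*Protocol*

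**What the plan says.** Three places in the protocol bear on this.

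- **Section 5.e, severity, relationship and outcome.** The severity "of a clinical adverse event is to be scored according to the following scale". The table that follows has four rows: 1 mild, 2 moderate, 3 severe, 4 life-threatening. Grade 4 is described as "Patients at risk of death at the time of the event". The text below the table uses the top two grades together ("All grade 3-4 toxicities are considered" serious). It also asks for changes in severity to be documented, so that the duration of an event at each level can be assessed.
- **Section 5.e, Serious Adverse Events (SAE).** Of AEs and SAEs alike, it says: "They must be recorded in the AE/SAE CRF with the following information". The first item is "The severity grade (mild, moderate, severe". The same section separately gives "Is life threatening" as one of the criteria that make an event serious.
- **Section 5.a, maternal/foetal secondary endpoints.** Item 6 is "Frequency and severity of adverse events".

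**The concern.** The scale and the instruction for recording it do not match. An investigator who grades an event 4, as the scale requires, finds no such value among the categories the protocol prescribes for the form. The nearest available value is severe, which is already the label of grade 3.

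At stake is what can be reported later. Severity is part of a named secondary endpoint, and the protocol also wants duration by level. If grades 3 and 4 share one code, neither summary can tell an incapacitating event from one that put the woman at risk of death, and worsening from grade 3 to grade 4 leaves no trace in the field. An analysis plan cannot restore a distinction that the form did not collect. Under section 5.f, data go directly into the electronic database through mobile devices, so the pick-list may be the first record of the grade.

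**Working it through.** There is no stated figure to reproduce, and no sample size, power or event count enters. The check is a comparison of the two lists.

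| Level | Scale for scoring (severity heading, 5.e) | Severity field on the AE/SAE form (SAE heading, 5.e) |
|---|---|---|
| 1 | Mild | Mild |
| 2 | Moderate | Moderate |
| 3 | Severe | Severe |
| 4 | Life-threatening | no entry |

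1. **Count.** The scale has 4 categories and the form field has 3, so 4 − 3 = 1 category has no entry. It is grade 4.
2. **Is grade 4 in use?** Yes. The same section refers to grades 3 and 4 together when it says which toxicities count as serious, so grade 4 is a working category.
3. **Is the form list binding?** As worded, yes. It is introduced as information that must be recorded, it covers both AEs and SAEs, and it uses the term severity grade, which points to the same quantity as the scale.
4. **Is there a mapping?** No. The protocol does not call the three-level list an example, and does not say that grade 4 is to be entered as severe.
5. **What follows if the form is built to the list?** Grades 1 and 2 keep their own codes. Grades 3 and 4 share the code severe. Endpoint 6 and duration by level are then available on three levels, not four.
6. **What is still captured elsewhere?** A life-threatening event meets a seriousness criterion of its own and so is an SAE. All SAEs go on the SAE form and are reported to the sponsor's safety coordinator, the CRO and the DSMB (monitoring and reporting of adverse events, 5.e). A death is recorded under the outcome classification. The seriousness criterion does not replace the grade, because it marks an event as serious without giving its severity over time, and it is not among the three items listed for the form.

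**The case against.** The best reply is that the three-item list is not a full specification of the form. Other parts of section 5.e require the action taken, changes in severity and the outcome to be documented, and none of these is in the list, so the form must hold more than it names. The protocol also leaves a toxicity table to an SOP, and section 5.g leaves adverse event assessment procedures to electronic SOPs. On that reading the bracketed words are shorthand for the four-grade scale, and the form as built may be correct. Part of this stands: neither the form nor the SOP is available, so the point concerns what the protocol prescribes and not what was programmed. It does not remove the conflict. The list may omit other items, but for severity it states the categories, and those differ from the scale.

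Three stronger readings are tempting, and the documents do not support them.

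- **Relationship to study drug.** The same list has "Relationship to the study drug(s) (suspected/not suspected", while the protocol defines five levels of relationship. A reader might infer that the boundary needed to identify a SUSAR is lost. It is not. The SUSAR definition counts possible, probable and definite as suspected, so the two-level field falls exactly between unlikely and possible. Severity has no such mapping.
- **DSMB reporting.** A reader might infer that the DSMB would receive a severity table in which grades 3 and 4 are mixed. No such table is described. The DSMB reviews all collected clinical safety data, and SAEs are reported to it.
- **Every grade 4 event misrecorded.** This would be so only on a form built strictly to the list. The form is not shown and no number of grade 4 events is given, so no proportion can be stated as fact.

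**Conclusion.** The point holds as an internal inconsistency of minor severity. The protocol requires four severity grades for scoring and prescribes three for recording, and it is life-threatening that drops out. If the form follows the prescription, grades 3 and 4 cannot be separated in the severity field. That affects endpoint 6, one of eleven maternal/foetal secondary endpoints, and the duration of events at each level.

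The size is one category of four in one field. How many events that would touch is unknown, because the protocol gives no expected number of grade 4 events, and it may be few. The primary endpoint, the sample size and the efficacy analysis do not depend on this field. Identification and reporting of life-threatening events as SAEs are intact.

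The conclusion assumes that the form is built as the SAE section states and that no SOP overrides it. If the form already carries grades 1 to 4, only the protocol text needs correcting.

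**What to change.** In the SAE section of 5.e, replace the three-level severity item with grades 1 to 4, using the labels and descriptions already in the severity table, and build the form's severity field to match. Tabulate endpoint 6 by those four grades in each arm, and use the same grades for duration at each level. The relationship field can stay as it is for this purpose.

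Before the form is built, the cost is one pick-list and one line of protocol text. If a three-level field is already in use, the database would have to be changed and every event entered as severe reviewed individually to recover its grade, so the correction is best made early.

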#### *Definition of Suspected Unexpected Serious Adverse Reaction (SUSAR):*

A serious adverse event (SAE) becomes a SUSAR (suspected unexpected serious adverse reaction) if the event is suspected (possibly, probably or definitely) to be related to the study drug and unexpected i.e. not previously documented in any of the product information or protocol.

#### **Data Safety Monitoring Board (DSMB)**

A Data and Safety Monitoring Board (DSMB) will be constituted previously to trial's initiation to review and analyse all collected clinical safety data and to assess unexpected AEs and SAEs. The DSMB will be an independent committee consisting of experts in infectious diseases, obstetrics, epidemiology, pharmacology, biostatistics and other appropriate disciplines that will be appointed to oversee ethical and safety aspects of the conduct of the trial.

The DSMB will review the implementation and progress of the study, providing advice on safety-related issues before the initiation of the study, during the study and at the close out of the study. Its advice will be based on the interpretation of study data with reference to the study protocol. The DSMB will be empowered to put the study on hold pending review of potential safety issues.

The DSMB will be informed by the Safety Coordinator of all protocol amendments, informed consent changes or revisions of other documents originally submitted for review, of all subsequent protocol modifications (for information) and of new information that may adversely affect the safety of the subjects or the conduct of the study. The DSMB will also review and approve Safety Reports submitted by the Safety Coordinator. All documentation provided to members of the DSMB for information and review will be treated in a confidential manner.

